### 9.2 Sample Size and Power Considerations

#### 9.2.1 Assumptions and Study Hypothesis:

- a. **Time to discharge or clinical improvement by 2 points** in the standard of care arm is expected to be (median: 11 days; Cai Q, Y.M., Liu D, Chen J, Shu D, Xia J, , Experimental Treatment with Favipiravir for COVID-19: An Open-Label Control Study. 2020.).
- b. The exact treatment effect from Favipiravir tables + Hydroxchloroquine is not exactly known but can be approximated using prior clinical studies. A study comparing the effect of Favipiravir to lopinavir/ritonavir on virus clearance has shown a 64% reduction in time to viral clearance in the Favipiravir arm. This was equivalent to a median of 11 days. We assume that clinical improvement might take place a little later to viral clearance and therefore we assume that the treatment arm might result in a minimum clinically meaningful expected reduction of 30% (Median 7.7 days). This is equivalent to a Hazard ratio of 0.7.

- c. We further assume, that 50% of the patients in the control group will have clinical improvement/ discharged and 70% will have clinical improvement/discharged in the treatment arm
- d. It is anticipated that very few of these subjects will be randomized and not start study treatment (and so be excluded from the primary analysis) or be lost to follow-up (and so have missing data for the primary endpoint). Given certain uncertainties however, we have included a nominal 10% drop out rate.
- e. The primary hypothesis of the current study is  $H_0: HR = 1$  vs.  $H_1: HR \neq 1$  ; and HR is the hazard ratio of treatment compared to control arm.

#### 9.2.2 **Sample Size Estimation for Classical Two Arm Parallel Design:**

Under the classical two arms parallel design the total effective sample sizes needed is 472 subjects (236 subjects per group). The Estimated sample size achieve 85 % power to detect a minimum of 30% reduction in the median time, to clinical improvement by at least two points or hospital discharge, in the treatment group compared to the control group. The median time in the treatment arm is 11 days under the null hypothesis and 7.7 days under the alternative hypothesis. The median time in control group under the null hypothesis is 11 days. The two survival curves will be analyzed using one sided cox proportional hazard regression. The significance level of the test is 0.025. Assuming 10% drop out rate, the overall sample size for the trial is estimated to be 520 (260 per group). Sample size adjustment will be considered after interim analysis of 60% of the subjects' recruitment and based on DSMB recommendation.

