### 9.3 Study Interim Analysis

The current study will have a single interim analysis which will take place at the completion of the recruitment and follow-up of 60% of the total number of subjects (i.e. 312). The interim analysis is designed to test for early stopping for futility or efficacy as well as for sample size re-estimation. The interim analysis and final analysis will be based on the method of the sum of the stage wise p-value discussed in Mark and Chang, 2008. The table below, describe the interim analysis testing boundaries.

| Boundary      | Decision                                                                                                       |
|---------------|----------------------------------------------------------------------------------------------------------------|
| Alpha1 = 0.01 | Stop the trial for early efficacy if the interim analysis p-value is less than 0.01                            |
| Beta1 =0.25   | Stop the trial for futility if the interim analysis P-value is equal to or larger than 0.25                    |
| Alpha2=0.1832 | Declare the trial significant if the sum of the interim analysis and final stage P-values are less than 0.1832 |

The sample size Re-estimation will be based on the ratio of the planned effect size to the observed effect size from the interim analysis according to the following formula:

$$N = \left( \frac{E_0}{E} \right)^a N_0$$

Where a is a constant which will be set to 2 and  $N_0$  is a number chosen to be slightly larger than the classical sample size per group,  $E_0$  is the planned effect size of .7 and E is the observed effect size from the interim analysis.

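### The 85% power in section 9.2.2 is for a single-look test; for the two-stage test in section 9.3 none is stated, and it is about 82% at 10% loss if the sample size is not increased

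*Protocol*

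**What the plan says.** Protocol section 9.2.1 sets the planning inputs. Of the 30% reduction in median time (11 to 7.7 days) it says "This is equivalent to a Hazard ratio of 0.7". For event proportions it assumes that "50% of the patients in the control group will have clinical improvement/ discharged and 70% will have clinical improvement/discharged in the treatment arm". It calls the 10% drop-out rate nominal and expects very few losses.

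Section 9.2.2 says that under the classical parallel design "the total effective sample sizes needed is 472 subjects (236 subjects per group"), and that "The Estimated sample size achieve 85 % power to detect a minimum of 30% reduction in the median time". The test is stated as "The two survival curves will be analyzed using one sided cox proportional hazard regression", and "The significance level of the test is 0.025". The step to the enrolled number is "Assuming 10% drop out rate, the overall sample size for the trial is estimated to be 520 (260 per group"). The same section says that a sample size adjustment will be considered after the interim, on the data monitoring board's recommendation.

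Section 9.3 then sets a different test for both the interim and the final analysis. After 60% of subjects (312), the trial stops for efficacy if the interim p-value is below 0.01 and for futility if it is 0.25 or more. At the end the rule is "Declare the trial significant if the sum of the interim analysis and final stage P-values are less than 0.1832". The section adds a re-estimation formula, N = (E0/E)^a x N0, with a = 2 and a planned effect size E0 of 0.7.

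**The concern.** The enrolled number and its headline power come from a test that will not be used for the final decision. Splitting the data at 60% and adding the two stage-wise p-values is less efficient than one Cox test on all the data at the same overall level. A sponsor, ethics committee or monitoring board reading 85% next to 520 will take the type II error as 15%. If the sample size stays as planned and the planned 10% is lost, it is nearer 18%.

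The drop-out step points the same way. Multiplying by 1.1 does not offset a 10% loss, so the enrolled number leaves slightly fewer evaluable patients than the plan says it needs.

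**Working it through.** **Inputs.** Hazard ratio 0.7, so |ln 0.7| = 0.3567 (9.2.1). Event proportions 50% and 70%, mean 60% (9.2.1). One-sided level 0.025 (9.2.2). Allocation 1:1 (section on randomization). Limits 0.01, 0.25 and 0.1832, look at 60% (9.3).

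**1. The plan's own figure.** Schoenfeld events for 85% power: 4 x (1.960 + 1.036)^2 / 0.3567^2 = 282.3, rounded up to 283. Patients: 283 / 0.60 = 471.7, so 472. The protocol's number reproduces. Single-look power is Phi(0.3567 x sqrt(D/4) - 1.960), where D is the number of events:
- 472 evaluable, D = 283.2: Phi(3.001 - 1.960) = 85.1%.
- 468 evaluable, D = 280.8: Phi(2.988 - 1.960) = 84.8%.

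**2. Drop-out.** 472 x 1.1 = 519.2, which gives 520. Allowing for 10% loss takes 472 / 0.9 = 524.4, so 525 (526 as 263 per arm). With 520 enrolled, 520 x 0.9 = 468 remain. The cost is 85.1 - 84.8 = 0.3 points.

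**3. Level of the two-stage test.** 0.01 + 0.5 x (0.1832 - 0.01)^2 = 0.0250. The limits control the one-sided level at 0.025, which confirms how they should be read: two independent stages, with the second p-value from the post-interim data only.

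**4. Power of the two-stage test, sample size as planned.** The stage means are 0.3567 x sqrt(0.6D/4) and 0.3567 x sqrt(0.4D/4). Power = P(p1 < 0.01) + P(0.01 <= p1 < 0.1832 and p1 + p2 < 0.1832). A trial with p1 between 0.1832 and 0.25 continues but cannot succeed, so it counts as a failure. At 468 evaluable the stage means are 2.315 and 1.890, and the two terms are 49.5% and 32.1%.

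| Evaluable | Loss from 520 | Single look | Two-stage, no increase |
|---|---|---|---|
| 468 | 10% | 84.8% | 81.6% |
| 472 | – | 85.1% | 81.9% |
| 494 | 5% | 86.7% | 83.6% |
| 520 | none | 88.3% | 85.4% |

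The two-stage rule costs about 3 points at each size. Holding 85% under it without an increase takes about 514 evaluable patients, or 514 / 0.9 = 572 randomised at 10% loss.

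**5. Re-estimation.** At 468 evaluable the interim has 0.6 x 280.8 = 168.5 events. A trial that continues (p1 from 0.01 to 0.25) then has an observed hazard ratio of about 0.70 to 0.90. With E0 = 0.7 and E taken as the hazard ratio in the same direction, (0.7/E)^2 runs from about 1.0 at E = 0.70 down to about 0.6 at E = 0.90. A weaker effect therefore gives a smaller trial. Power stays at 81.6% if the sample size may not fall below plan. It is about 72% if it may, taking N0 as 480 randomised in total.

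On a scale where a weaker effect is a smaller number, such as log hazard ratio or one minus hazard ratio, N does rise. With the same N0 and no decrease allowed, power is about 86% with a cap of 1.25 times the plan, 88% with 1.5 times and 89% with 2 times. Section 9.3 names none of these scales and sets neither floor nor cap.

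**The case against.** The strongest reply is that section 9.2.2 labels 85% as the classical design's power, and for that design it is correct. This stands: the figure is not miscalculated. What is missing is a power figure for the test that section 9.3 puts in its place.

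A reader might infer that the drop-out slip by itself defeats the 85%. It does not: 84.8% still rounds to 85%, and the shortfall is five or six patients in about 520.

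A reader might also infer that the trial's interim rules leave it at 81.6%, full stop. The documents do not support that. The figure leaves out re-estimation, which is one of those rules, and it assumes the full nominal 10% loss, with lost patients contributing nothing. Section 9.2.1 expects very few losses, and section 9.4 censors lost patients at last contact, so they do contribute follow-up. With negligible loss the two-stage power is back at about 85%.

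The opposite reading, that re-estimation secures the 85%, is not supported either. An adjustment is only to be considered, and the formula as written does not usefully raise the sample size in a trial that continues.

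Finally, the sensitivity analysis in 9.2.2 already reports power from 78% to 90% and treats 80% as the accepted norm, so 81.6% is not alarming in itself. That range comes from varying event proportions, though, not from the interim test, so it does not disclose this loss.

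**Conclusion.** The point holds in limited form. The stated 85% is correct for 472 evaluable patients under a single-look Cox test, but no power is given for the two-stage test that will decide the trial. With no increase in sample size, that power is about 81.6% at the planned 10% loss (type II error about 18% instead of 15%), 83.6% at 5% loss and 85.4% with none.

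These figures assume a hazard ratio of 0.7, a 60% mean event proportion, 60% of the events at the interim and independent stages. Re-estimation could take power above 85%, but only on an effect scale that section 9.3 does not specify and with increases allowed. The inflation by 1.1 is a genuine but minor slip worth about 0.3 points.

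**What to change.** In section 9.2.2:
- Keep 520 and state that 10% loss leaves 468 evaluable patients.
- Keep 85% only as the classical-design figure for 472.
- Beside it, give the power of the two-stage design: about 82% at 10% loss with no sample size increase, and up to about 85% with negligible loss.

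Claim a higher power only after section 9.3 defines the re-estimation effect scale, the floor and the cap.

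This is a wording change and needs no more patients. Its price is a stated power about 3 points less favourable at the planned drop-out rate.

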## Sensitivity analysis

We have performed several sensitivity analyses to determine the effect of different assumptions on the sample size. Figure 2A, shows the relationship between the proportion of event in the treatment (Pev2), the proportion of event in the control (Pev1) and the power of the study. Increase in the events in both groups lead to increase in the overall study power up to 90%. Simultaneous decrease in the events could lead less of power to as low as 78%. Reduction of events in the treatment group alone does not lead to loss of power below the accepted norm of 80%. Because reduction in the proportion of events in treatment group has the largest impact, we examined the impact of overestimation of the HR and the proportion of events in the treatment group on power. Figure 2B, shows that regardless of the number of events a slight change in the HR than the assumed will have severe impact on power. However, the current design could accommodate an overestimation of HR by only 10% (.27 instead .3) before power falls under desired level.

[figure not shown]

Figure 2 . A: Impact of proportion of events in treatment and control on Power. B: Impact of HR and proportion of events in treatment arm on power.

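### The claim that fewer treatment-arm events alone cannot take power below 80% rests on holding the hazard ratio at 0.7; with control at 50% and the hazard ratio implied by the proportions, power is about 61% at 60% and 20% at 55%.

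*Protocol*

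**What the plan says.** Section 9.2.2 of the Protocol sets the design: "the total effective sample sizes needed is 472 subjects (236 subjects per group"), and "The Estimated sample size achieve 85 % power to detect a minimum of 30% reduction in the median time". On the test it says "The two survival curves will be analyzed using one sided cox proportional hazard regression" and "The significance level of the test is 0.025". Section 9.2.1 gives the planning values: 50% improved or discharged in control, 70% on treatment, and a 30% shorter median, of which it says "This is equivalent to a Hazard ratio of 0.7". It also expects very few patients to be lost. Section 9.4 censors everyone who completes follow-up at day 28.

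The sensitivity analysis then varies the two event proportions (Figure 2A, not reproduced in the text available). Power rises to 90% when both go up and falls to 78% when both go down. For a fall in one arm only it concludes: "Reduction of events in the treatment group alone does not lead to loss of power below the accepted norm of 80" per cent. The next sentence begins "Because reduction in the proportion of events in treatment group has the largest impact" and introduces Figure 2B, which varies the HR together with the treatment-arm proportion. The text on Figure 2B warns that small departures from the assumed HR harm power badly. It adds that the design can tolerate a 27% rather than a 30% reduction before power drops under the desired level.

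**The concern.** In many survival trials the event proportion is a nuisance quantity: fewer events mean less information about an effect of given size. Here the event is the benefit itself. If the control arm stays at 50% by day 28 and fewer than 70% improve on treatment, the treatment is doing less than assumed. A sensitivity analysis that lowers the treatment-arm proportion while leaving the HR at 0.7 counts the lost events but not the lost effect.

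The sentence carries no condition. A sponsor, ethics committee or DSMB judging whether 520 patients suffice could take it to mean that power stays acceptable even if treated patients do less well than hoped.

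**Working it through.** **Inputs.** 236 per group, one-sided 0.025 (section 9.2.2); 50% and 70% events and HR 0.7 (section 9.2.1); 1:1 allocation (randomization section); common 28-day horizon (section 9.4).

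On direction: section 9.2.1 says "HR is the hazard ratio of treatment compared to control arm". With improvement as the event, a beneficial HR on that definition would exceed 1 (1/0.7 = 1.43). I keep the protocol's 0.7 scale, which is control over treatment. Power depends only on |ln HR|, so the results are the same either way.

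**Formula (Schoenfeld).** Events D = 236 × (pC + pT). Power = Φ(½√D × |ln HR| − 1.96). For HR 0.7, |ln HR| = 0.3567.

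**Step 1: reproduce the plan.** Base case: D = 236 × 1.2 = 283.2; ½ × 16.83 × 0.3567 = 3.00; Φ(3.00 − 1.96) = 85.1%. Holding HR at 0.7 throughout:

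| pC / pT | D | Power at HR 0.7 | Plan states |
|---|---|---|---|
| 50 / 70 | 283.2 | 85.1% | 85% |
| 60 / 80 | 330.4 | 90.0% | up to 90% |
| 40 / 60 | 236.0 | 78.2% | as low as 78% |
| 50 / 60 | 259.6 | 81.9% | not below 80% |
| 50 / 55 | 247.8 | 80.2% | not below 80% |
| 50 / 50 | 236.0 | 78.2% | – |
| 40 / 70 | 259.6 | 81.9% | – |

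The three stated figures match, so the HR was held at 0.7. The 50/50 row shows the consequence: 78% power with no difference between the arms at day 28.

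**Step 2: let the HR follow the proportions.** Under proportional hazards with everyone followed to day 28, HR = ln(1 − pC) / ln(1 − pT). With control at 50%:

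| pT | Implied HR | D | Power |
|---|---|---|---|
| 65% | 0.660 | 271.4 | 92.8% |
| 62.4% | 0.709 | 265.2 | 80.0% |
| 60% | 0.756 | 259.6 | 61.3% |
| 55% | 0.868 | 247.8 | 19.9% |

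For 60%: ½ × 16.11 × 0.2791 = 2.249; Φ(0.289) = 61.3%. Log-rank simulation (4,000 trials each, exponential times) gave 60.7% at 60% and 20.0% at 55%. A two-proportion test gives 58.9% and 19.1%. With all 520 analysed, power is 65.5% and 21.5%.

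**Step 3: a different anchor.** Step 2 does not pass through the plan's base case: 70% v 50% implies HR 0.576 and power 99.6%, not 85%. Suppose instead that HR 0.7 is kept at 70% and the log HR is halved when the difference is halved. At 60%, |ln HR| = 0.178, and Φ(8.056 × 0.178 − 1.96) is about 30%.

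**Step 4: the neighbouring statements, on the plan's own fixed-HR formula.** With 1:1 allocation power depends on pC + pT only, so 50/60 and 40/70 give the same 81.9%. Neither arm has the larger impact. For a 27% reduction, HR = 0.73 and |ln HR| = 0.3147. At 50/70, power = Φ(½ × 16.83 × 0.3147 − 1.96) = Φ(0.688) = 75.4%. With all 520 analysed it is 79.4%.

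**The case against.** The strongest reply is that the sensitivity analysis has two parts. Figure 2A isolates event counts, Figure 2B takes up the HR, and the text on Figure 2B says plainly that a slightly smaller effect damages power severely. A reader might infer from the disputed sentence that the protocol hides its sensitivity to a weaker effect. It does not. But it treats the HR and the treatment-arm proportion as separate inputs, never connects them, and leaves the robustness sentence unqualified.

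A reader might also take 61% as the trial's true power at 60% v 50%. The documents do not support that. The same scenario gives about 82%, 61% or 30% depending on whether the HR is fixed, implied by the proportions, or shrunk from the plan's anchor. Nor is the move from 85% to 61% one coherent curve, because the implied-HR model gives 99.6% at the base case. On that model a moderate fall, from 70% to 65%, still leaves 93%.

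Three further limits stand. If treatment-arm events fell only because of early censoring, the HR could remain 0.7 and the sentence would hold down to about 55%; the protocol expects little such loss. Figure 2A is not available, and its stated figures suggest a range of about 60% to 80% on treatment, so the 55% row may lie outside what was plotted. Finally, these are single-look figures, as is the plan's 85%. The interim futility rule and sample size re-estimation in section 9.3 would change the operating power.

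The complaint about the largest-impact statement applies only under the fixed HR. With the HR tied to the proportions, a fall in the treatment arm does matter more: 50/60 gives 61%, and 40/70 gives over 99.9%.

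**Conclusion.** The point holds. The robustness sentence describes a calculation with the HR fixed at 0.7, which it does not say, and the design lacks the property claimed. With control at 50%, power passes below 80% at about 62% improved on treatment, and is about 61% at 60% and 20% at 55%. This assumes proportional hazards, near-complete follow-up to day 28, 472 evaluable patients and a single look. The alternative anchor gives a lower value at 60%, about 30%, so the conclusion that power is below 80% there does not depend on which of the two linked models is used.

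Two nearby statements fail on the protocol's own formula: the largest-impact claim (82% either way) and the tolerance for a 27% reduction (75% with 472 evaluable, and just under 80% even with 520).

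The underlying cause is that 50%, 70% and HR 0.7 do not fit together under proportional hazards. 70% v 50% implies HR about 0.58. HR 0.7 with 50% in control implies 1 − 0.5^(1/0.7), about 63% on treatment, with power about 83%. None of this shows that 520 patients is the wrong number; it shows that the stated robustness is too favourable.

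**What to change.** 1. Withdraw the robustness sentence, or limit it to the case where the HR is held at 0.7 and events are lost through censoring only.
2. Take the control proportion and the HR as the two inputs and derive the treatment proportion as pT = 1 − (1 − pC)^(1/HR), on the 0.7 scale. Redraw Figures 2A and 2B on that basis.
3. State in section 9.2.1 that 50%/70% and HR 0.7 are not mutually consistent under proportional hazards, and restate the base case. With 50% in control and HR 0.7 it is about 63% on treatment and 83% power.
4. Restate the 10% tolerance. On this basis HR 0.73 with 50% in control gives pT 61.3%, D = 262.7 and power about 72%. Say what the desired level is.
5. Remove the largest-impact statement or rederive it from the new figures.
6. Name the assumptions: proportional hazards, 28-day follow-up, number evaluable, single look.

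The cost is a reworked base case, two figures and a few sentences. No patients are added. The stated robustness becomes less favourable.

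### The stated tolerance of a 27% instead of a 30% reduction is wrong: on the plan's own inputs power there is 75%, below both 80% and 85%

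*Protocol*

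**What the plan says.** Section 9.2.2 fixes the design: "the total effective sample sizes needed is 472 subjects (236 subjects per group"), with this claim: "The Estimated sample size achieve 85 % power to detect a minimum of 30% reduction in the median time". On the test it states "The two survival curves will be analyzed using one sided cox proportional hazard regression" and "The significance level of the test is 0.025". Section 9.2.1 sets the effect, saying of the 30% reduction in the median: "This is equivalent to a Hazard ratio of 0.7". It sets the event rates by assuming that "50% of the patients in the control group will have clinical improvement/ discharged and 70% will have clinical improvement/discharged in the treatment arm".

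The sensitivity analysis then varies these inputs. It reports power of up to 90% with more events in both groups, and as low as 78% with fewer in both. With fewer events in the treatment group alone, it says, power does not drop "below the accepted norm of 80" per cent. It warns that a small change in the hazard ratio affects power severely, and closes with the tolerance: "the current design could accommodate an overestimation of HR by only 10% (.27 instead .3) before power falls under desired level". It does not say whether the desired level is 80% or 85%, nor which sample size and event rates lie behind the 27%.

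**The concern.** The 472 subjects were sized for 85% power at a hazard ratio of 0.70, so the design has little room before power reaches 80%. Power responds steeply to the hazard ratio, and a move from 0.70 to 0.73 looked too large to leave it at 80%.

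This sentence is the only figure the protocol gives for how far the effect may fall short. Section 9.2.1 concedes that the effect is not exactly known and approximates it from viral clearance in another comparison, so a shortfall is plausible. If the margin is overstated, readers will think the trial safer against an optimistic effect assumption than it is.

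**Working it through.** **Inputs, all from the protocol**
- One-sided significance level 0.025 (9.2.2), so z = 1.960.
- 236 evaluable subjects per group (9.2.2), allocated 1:1 (Randomization section).
- Event proportions 0.50 and 0.70 (9.2.1): 236 × 0.50 + 236 × 0.70 = 283.2 events.
- Design hazard ratio 0.70 (9.2.1); claimed tolerable hazard ratio 1 − 0.27 = 0.73.

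**Formula** (Schoenfeld, equal allocation, d events): power = Φ(−ln(HR) × √d / 2 − 1.960).

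**Step 1: reproduce the plan's figures at HR 0.70**
- Planned events: 0.3567 × √283.2 / 2 = 3.001; 3.001 − 1.960 = 1.041; power 85.1%. The plan states 85%.
- In reverse, 85% power needs 283 events, and 283 / 0.60 = 471.7, so 472 subjects. The plan states 472.
- Both event proportions raised by 0.10 (330.4 events): 90.0%. The plan states up to 90%.
- Both lowered by 0.10 (236 events): 78.2%. The plan states as low as 78%.
- Treatment arm alone lowered to 0.60 (259.6 events): 81.9%. The plan says it stays above 80%.

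The shift of 0.10 is an assumption, because Figure 2 is not available. With it, every other figure in the section is recovered at 472 subjects.

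**Step 2: power at the claimed tolerance, HR 0.73**
- 0.3147 × √283.2 / 2 = 2.648; 2.648 − 1.960 = 0.688; power 75.4%.
- Freedman's form replaces −ln(HR) / 2 with (1 − HR) / (1 + HR) and gives 74.7%.

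**Step 3: the tolerance the design does have**
- 80% power: HR = exp(−2 × (1.960 + 0.842) / √283.2) = 0.717, a 28.3% reduction. From the unrounded value 0.7168, the relative shortfall is (0.3000 − 0.2832) / 0.3000 = 5.6%.
- 85% power: HR = 0.7004, so practically no shortfall.

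**Step 4: other settings, single look, one-sided 0.025**

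| Setting | Events | Power at HR 0.70 | Power at HR 0.73 |
|---|---|---|---|
| 472 subjects, mean event rate 50% | 236.0 | 78.2% | 67.6% |
| 472 subjects, mean event rate 60% (plan) | 283.2 | 85.1% | 75.4% |
| 472 subjects, mean event rate 70% | 330.4 | 90.0% | 81.6% |
| All 520 subjects, mean event rate 60% | 312.0 | 88.3% | 79.4% |

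Taking the 10% off the log hazard ratio instead (HR 0.725) gives 77.1% at 283.2 events. A one-sided 0.05 test would give 84.2% at HR 0.73, but 91% at HR 0.70, which contradicts the stated 85%.

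**Step 5: the two-stage rule of section 9.3.** Simulated with the boundaries 0.01, 0.25 and 0.1832, the interim at 60% of 283.2 events and no sample size re-estimation, power is 82.0% at HR 0.70 and 71.7% at HR 0.73.

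**The case against.** The strongest defence is that the sentence summarises Figure 2B, which cannot be seen, and may rest on unstated inputs. Overestimating an effect by 10% could mean 0.30 / 1.1 = 0.273, rounded to 0.27. At a hazard ratio of 0.727 with all 520 subjects (312 events), power is 80.3%. With 312 events power crosses 80% at a 27.2% reduction, a shortfall of 9.4%, close to the claimed 10%. Section 9.2.1 calls the 10% dropout nominal and expects very few losses, so a run at 520 is conceivable.

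This may explain where the figure came from, but it does not make the sentence right. At the 27% actually printed, 520 subjects give 79.4%, still under 80%. That basis also implies 88% power at a hazard ratio of 0.70, whereas the section's other figures fit 472. With 472 subjects even 0.727 gives only 76.4%. The claim does pass 80% at a mean event rate of 70% (81.6%), but that changes a second assumption in the trial's favour.

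Three points of the defence stand in part.
- A design target of 85% and a floor of 80% can coexist. What is missing is a statement of which one is the desired level. Since 472 was sized for 85%, the lack of slack against 85% follows by construction, and the comparison with 80% carries the weight.
- The paragraph already warns that power is fragile, and no interim decision in section 9.3 rests on this sentence.
- The two-stage figure leaves out re-estimation, so it shows only the direction of the effect before any increase in sample size.

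**Conclusion.** The stated tolerance is wrong. On the protocol's inputs, power at a 27% reduction is 75% (75.4% by Schoenfeld, 74.7% by Freedman): about 5 percentage points under the 80% norm and 10 under the 85% target. The design keeps 80% power down to a 28.3% reduction, a relative shortfall of 5.6%, so the stated 10% is nearly twice the true margin (10 / 5.6 = 1.8).

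This assumes a single-look test at one-sided 0.025, 472 evaluable subjects, event rates of 50% and 70%, and the 27% read as a hazard ratio of 0.73. The first three are the inputs that reproduce the stated 85%. The conclusion changes only with event rates better than planned, or with all 520 subjects combined with a reduction of 27.2% or more.

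The error does not touch the calculation of 472 or 520 subjects, any boundary or any analysis. It should be corrected because the protocol states a power property that the design does not have.

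**What to change.** Replace the sentence with, for example: *With 472 evaluable subjects and 283 events, power is 75% at a 27% reduction (hazard ratio 0.73). It falls below 80% when the reduction is under 28.3% (hazard ratio above 0.717).* State whether the desired level is the 85% target or the 80% floor, and use that term in the same way in both places. If the 27% was read from Figure 2B on another basis, give the sample size and event rates behind it. Say also that the figures are for a single-look design, because section 9.3 adds a two-stage rule.

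The cost is two corrected sentences and a less favourable figure, with no change in sample size. If the sponsor instead wants the margin as now stated, a hazard ratio of 0.73 needs 317 events (about 529 evaluable subjects at a 60% mean event rate) for 80% power, or 363 events (605 subjects) for 85%, in a single-look design.
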